### Diagnostic accuracy

[^68^Ga]Ga-FAPI-46 PET/CT images will be independently interpreted under standardized conditions by two experienced nuclear medicine physicians, considering the currently known pitfalls in FAPI imaging [57–59]. The interpreters will be blinded to all clinical information regarding the patients except for the cancer diagnosis. Any disagreements that arise will be resolved through a consensus-based approach. Likewise, the [^18^F]FDG PET/CTs will be interpreted under standardized condition by experienced nuclear medicine physicians. ceCTs performed at primary staging and at post-NACT staging is part of the PET/CT procedure and will also be available for the interpreters and be used for deeming malignancy in suspicious lesions with low [^18^F]FDG / [^68^Ga]Ga-FAPI-46 uptake.

The correlations of the PET/CT results with histopathology, estimated sensitivities, specificity, PPV, and NPV for [^68^Ga]Ga-FAPI-46 PET/CT and [^18^F]FDG PET/CT findings will be compared for primary tumors, lymph nodes and distant metastases (e.g., peritoneal metastases). Ultimately, the diagnostic accuracy of [^68^Ga]Ga-FAPI-46 PET/CT and [^18^F]FDG PET/CT will be compared at primary staging and post-NACT-staging. Suspicious tumor lesions revealed on [^68^Ga]Ga-FAPI-46 PET/CT lacking histopathological confirmation will be evaluated using available routine diagnostic images ([^18^F]FDG PET/CT, UL, MR, ceCT), medical records, and laboratory tests. Furthermore, correlating [^68Ga^]Ga-FAPI-46 PET/CT at post-NACT staging with histopathology will be useful for assessing the feasibility of [^68^Ga]Ga-FAPI-46 PET/CT after chemotherapy.

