**Fig. 1 Fig1:**
[figure not shown]
FAPI PET in ovarian cancer study design and flow

[^68^Ga]-Ga-FAPI-46 PET/CT data will be interpreted after enrollment of all patients and compared to the [^18^F]-FDG PET/CT data. Histopathology of the resected specimens and biopsies will serve as a reference standard for calculating the diagnostic accuracy. For suspicious lesions not confirmed by histopathology, other imaging modalities (US, MRI, CT), biochemistry, and medical records will be used for classification. The clinical impact of [^68^Ga]Ga-FAPI-46 PET/CT, both at primary staging and post-NACT staging, will be evaluated at a retrospective tentative MDT with the participation of an onco-gynecological surgeon, an oncologist, a pathologist, and a nuclear medicine physician, all of which specialize in the treatment of ovarian cancer. The tentative MDT will be performed retrospectively and therefore has no influence on the actual treatment of patients; moreover, the MDT differs from the clinical MDT, as clinicians will present study-related [^68^Ga]Ga-FAPI-46 PET/CTs instead of [^18^F]FDG PET/CTs. The study flow is depicted in Fig. 1.

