### Imaging procedure

A dose of 200 *±* 50 Megabecquerel (MBq) [^68^Ga]Ga-FAPI-46 will be injected through an antecubital peripheral venous catheter. Patients will be encouraged to per-oral intake of water and instructed to empty their bladder immediately before PET/CT acquisition, which will be performed 30 *±* 5 min after tracer injection—no other patient preparation is needed. Before imaging, a scout scan will be performed to determine the scan area, which will be identical to the [^18^F]FDG PET/CT scan area. First, a low-dose CT scan (2–4 mSv) will be performed immediately followed by PET image acquisition. The scan procedure will last for approximately 25 min, after which the patients can immediately go home. Presently, there are no guidelines on how to perform a FAPI PET. The FAPI PET procedure used in the present study protocol is based on the best available evidence in the published literature and a systematic review conducted by the investigator [55]. The [^18^F]FDG PET/CT scan procedure will be performed in accordance with the dept. of Nuclear Medicines, Aalborg UHs local instructions and international guidelines [56]. Diagnostic ceCT covering the entire PET field-of-view is conducted as part of common clinical practice, both at primary staging and at post-NACT staging, and will be available when interpreting the PET scans.

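### The contrast-enhanced CT used in both PET/CT reads is also listed as fallback reference evidence, so at unsampled sites a CT-driven call can be confirmed by the same image

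*Protocol article*

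**What the plan says.** **Role in the index test.** Imaging procedure describes the ceCT as routine: "Diagnostic ceCT covering the entire PET field-of-view is conducted as part of common clinical practice". The scan is done at each of the two staging time points, and the PET readers have it in front of them. Diagnostic accuracy goes further. It states that "ceCTs performed at primary staging and at post-NACT staging is part of the PET/CT procedure", and that these scans "will also be available for the interpreters and be used for deeming malignancy in suspicious lesions with low" uptake of either tracer. For a low-uptake lesion, the ceCT can therefore produce the positive call in either read.

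**Role in the reference.** Study flow overview (text after Fig. 1) sets the main standard: "Histopathology of the resected specimens and biopsies will serve as a reference standard for calculating the diagnostic accuracy". The next sentence adds the fallback: "For suspicious lesions not confirmed by histopathology, other imaging modalities (US, MRI, CT), biochemistry, and medical records will be used for classification". Diagnostic accuracy has its own version. Suspicious lesions seen on FAPI PET/CT and "lacking histopathological confirmation will be evaluated using available routine diagnostic images"; the list that follows names FDG PET/CT, ultrasound, MR and ceCT, and then records and laboratory tests.

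**Sampling.** Pathology analysis says that the trial does not change how much tissue is taken, so sites not resected or biopsied in routine care stay without histology.

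**The concern.** A reference standard should not contain the test that it judges. If it does, calls made from the shared component tend to be scored correct (incorporation bias). Here the shared component is the ceCT. A low-uptake lesion at an unsampled site may be called malignant because of its appearance on ceCT, and then be classified as malignant because of that same appearance. A false positive is then counted as a true positive.

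Sensitivity, specificity, PPV and NPV are the primary objective. The Background criticises earlier FAPI studies because most findings beyond the primary tumour could not be compared with histopathology, and Sample size and patients justifies 50 patients partly by the validity of the accuracy estimates. A fallback that may reuse the index image weakens that claim at the very sites where tissue is missing.

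Two neighbouring issues are separate. One is that FDG PET/CT is itself in the fallback; removing it would leave the ceCT overlap in place. The other is that a shared ceCT may narrow the contrast between tracers; that concerns the difference, whereas this point concerns absolute accuracy.

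**Working it through.** The plan gives no figure for this point, so there is nothing to reproduce. The first step is textual, the second an illustration.

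**Step 1: the sections side by side**

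| Question | Where | Answer |
|---|---|---|
| Is ceCT part of the index read? | Diagnostic accuracy; Imaging procedure | Yes, for both tracers and both time points |
| Can it decide the call? | Diagnostic accuracy | Yes, for low-uptake suspicious lesions |
| Is it in the fallback for FAPI-suspicious lesions? | Diagnostic accuracy | Yes, by name |
| Is it in the fallback for other suspicious lesions, including FDG-only ones? | Study flow overview | CT is listed, without saying which CT |
| Is the scan already read excluded, or the fallback limited to later imaging? | Neither section | No |
| Do fallback-classified lesions enter the primary estimates? | Primary objectives; Study flow overview; Diagnostic accuracy | Not settled: the objectives name only histopathology, but the fallback directly follows the reference-standard sentence |

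The overlap is therefore permitted by the text as written. The protocol does separate information elsewhere: under Staging and impact on patient management, FDG results are withheld from the tentative MDT. No similar rule protects the reference standard from the index image.

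**Step 2: how large could it be?**

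None of these inputs is in the document; all are assumptions.

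- s = share of PET/CT-positive sites without tissue: 30 to 50%
- c = share of those calls that rest on ceCT: 20 to 40%
- p = true malignancy rate among those ceCT-driven calls: 50 to 70%
- q = share of the false positives among them that the fallback confirms because of the same ceCT: 0 to 1

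PPV inflation = s × c × q × (1 − p)

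| q | Low corner (s 0.3, c 0.2, p 0.7) | High corner (s 0.5, c 0.4, p 0.5) |
|---|---|---|
| 0 | 0 | 0 |
| 0.25 | 0.3 × 0.2 × 0.25 × 0.3 = 0.45 points | 0.5 × 0.4 × 0.25 × 0.5 = 2.5 points |
| 0.5 | 0.9 points | 5 points |
| 1 | 1.8 points | 10 points |

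With s = 0 the inflation is zero whatever the other inputs.

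**Cross-check with another parameterisation.** Let P be the true PPV over all positive calls, u the unsampled share of those calls, and q now the share of all unsampled false positives that are confirmed through the ceCT. Apparent PPV = P + u × q × (1 − P).

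- P = 80%: 0.80 + 0.1 × 0.25 × 0.20 = 80.5%, up to 0.80 + 0.5 × 1 × 0.20 = 90%.
- P = 90%: 0.90 + 0.1 × 0.25 × 0.10 = 90.25%, up to 0.90 + 0.5 × 1 × 0.10 = 95%.

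This gives 0.25 to 10 points, again with zero at u = 0.

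**Direction.** Self-confirmation can only move false positives into the true-positive cell. PPV rises. Specificity, TN / (TN + FP), rises too because FP shrinks.

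**The case against.** The strongest reply has five parts.

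1. **The fallback is a composite.** Ultrasound, MR, laboratory tests and records also count. A reader might infer that a ceCT-driven call is automatically confirmed by its own image. The documents do not say so; full circularity needs the ceCT to be the only or deciding evidence. This part stands, which is why the point says *can be* confirmed and why q is in the formula.
2. **The CT is undated.** FAPI scans are read only after all patients are enrolled, and follow-up runs for up to 10 years, so later CTs could serve. That is possible, but ceCT is both a routine image and a named fallback item, and nothing excludes the scan already read. The possibility of later imaging limits the problem without removing it.
3. **The primary estimates may be histology-only.** Primary objectives can be read that way, and the text does not settle it. So it cannot be asserted that the primary PPV and specificity will be overstated; they are biased only if fallback-classified lesions are counted.
4. **The scope is narrower for FDG.** The only fallback that names ceCT covers lesions suspicious on FAPI. FDG-only lesions come in through the generic CT in Study flow overview. This stands.
5. **The comparison is largely spared.** The truth label belongs to the lesion. Where ceCT drives both reads, both tracers get the same call and the same label. A reader might infer that the overlap favours FAPI; this mechanism gives no support for that. The trial is also described as exploratory and has no formal sample size calculation. This stands and lowers the severity.

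**Conclusion.** The point holds as a permitted overlap, not as a certain error. The ceCT can decide a positive call in both reads, and it is among the evidence that may classify the same lesion when tissue is missing. Where it is the deciding evidence, and such lesions are counted, PPV and specificity are biased upward.

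The size cannot be known from the document. It runs from zero (no unsampled positives, or a fallback that never relies on the same ceCT) to about 10 points of PPV under the assumed ranges with q = 1. The 1.8 points in the low corner should not be read as a floor, since it also assumes complete self-confirmation; nor should 10 points be read as an expected value. Lesions with histology are unaffected.

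Severity: should be fixed. It concerns the absolute accuracy figures in the primary objective, but the error is largely shared by both tracers in an exploratory comparison.

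**What to change.** **Change to make**

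- In Study flow overview and Diagnostic accuracy, state that the ceCT used in an index read may not serve as reference evidence for that lesion.
- Classify unsampled lesions from evidence used in neither index read: ultrasound or MRI, later routine imaging, later biopsy, clinical course. This wording also settles the listing of FDG PET/CT in one fallback and not in the other.
- Where no such evidence exists, classify the lesion as indeterminate.
- Report accuracy on histology-verified lesions and, alongside, on histology plus independent fallback. Add a sensitivity analysis with indeterminate lesions taken as all malignant and then as all benign. State which set supplies the primary estimates.

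**Timing.** FAPI reading starts only after full enrolment, so the rule can be fixed before any FAPI scan is interpreted.

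**Cost.** No new scans are needed. Some lesions lose their reference evidence: under the assumptions above, up to s × c of positive sites, that is 0.3 × 0.2 = 6% to 0.5 × 0.4 = 20%. PPV may look less favourable. The histology-only set has its own weakness, partial verification: tissue is taken in routine care, and treatment follows the conventional work-up, which includes FDG PET/CT and ceCT. Neither set is sufficient alone, so both should be shown.

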### Study objectives

#### Primary objectives

The primary objectives are to compare the FAPI PET/CT and FDG PET/CT findings in primary tumors, regional lymph nodes and distant metastases to a histopathological reference standard to the sensitivity, specificity, positive predictive value (PPV), and negative predictive value (NPV) of the PET/CTs, both at primary staging and post-NACT staging (i.e., staging after NACT, prior to interval debulking). This will include a comparison of the cancer stage determined by FAPI PET/CT and conventional imaging (including [^18^F]FDG PET/CT) at primary staging and post-NACT staging [50, 51]. The proportions of patients downstaged, having unchanged stage, and being upstaged according to the added FAPI PET/CT will be determined.

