### Study design

#### Study flow overview

This prospective study will comply with the Standard for Reporting Diagnostic Accuracy (STARD) criteria. Good Clinical Practice (GCP) will be followed to the extent that this is a diagnostic test accuracy trial involving an investigational medicinal product (IMP) [52].

Patients with newly diagnosed biopsy-verified OC *or* highly suspected OC (based on all the information presented at the Gynecological Cancer Multidisciplinary Team Conference (MDT)) with operable and resectable disease will be identified at the MDT. Based on the standard diagnostic workup, which includes [^18^F]FDG PET/CT and a diagnostic contrast enhanced CT (ceCT), and in line with national and international guidelines, patients will either go directly to surgery (Group A) or undergo neoadjuvant chemotherapy prior to surgery (Group B). Patients in both groups (A + B) will undergo FAPI PET/CT prior to treatment and within 1 week of receiving the primary FDG PET/CT (Fig. 1). The additional FAPI PET/CT will not interfere with or delay routine diagnostic workup or treatment, and the results of the FAPI PET/CT will not be available to the patient or the treating physician. Patients in Group B will undergo post-NACT-staging with conventional imaging (including [^18^F]FDG PET/CT) 2–3 weeks after NACT. In addition to conventional imaging, an additional blinded FAPI PET/CT will be performed at post-NACT staging.

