### Study-related procedures and data analysis

#### Pathology analysis

The clinical trial will not influence the amount of biological material collected from the patients. The surgical specimens will be divided into different containers during surgery and subsequently sent to the Dept. of Pathology, with labels indicating the exact location according to common clinical practice, enabling correct correlation of the histopathology of lesions to the imaging modalities. All surgical specimens will undergo histopathological examination according to routine clinical practice, with additional analyses, including quantitative evaluations of the density and intensity of FAP-expressing tumor cells or CAFs by applying immunohistochemistry. Standardized uptake values (SUVs) in tumor deposits will be compared to tumor characteristics, as determined by pathology, including immunohistochemistry.

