### Staging and impact on patient management

Tentative staging based on FAPI and [^18^F]FDG PET/CT data will be performed according to the International Federation of Gynecological Oncology’s classification system (FIGO) and the American Joint Committee on Cancer (AJCC 8th) edition TNM classification. Staging, as determined at the tentative MDT, will be compared for [^68^Ga]Ga-FAPI-46 PET/CT and [^18^F]FDG PET/CT, both at primary staging and post-NACT staging, and patients will be classified as “upstaged”, “unchanged”, or “downstaged” due to [^68^Ga]Ga-FAPI-46 PET/CT. The proportions of patients in these categories will be calculated. Furthermore, at the tentative MDT, the treatment strategy (e.g., operability, resectability, palliative treatment, other treatment) will be evaluated purely based on the [^68^Ga]Ga-FAPI-46 PET/CTs (replacing [^18^F]FDG PET/CTs) both at primary staging and at post-NACT staging. The proportion of patients with a hypothetically changed treatment strategy will be calculated. Supplementary imaging results (excluding the FDG PET/CT results), biochemical data, and medical records prior to the staging time point will be available for the clinicians attending the tentative MDT to mimic the situation at the clinical MDT.

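### The fallback reference for FAPI lesions without histology includes FDG PET/CT, the comparator, and contradicts the fallback stated elsewhere, so it can distort the primary accuracy comparison

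*Protocol article*

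**What the plan says.** Under Primary objectives, the stated aim is "to compare the FAPI PET/CT and FDG PET/CT findings in primary tumors, regional lymph nodes and distant metastases to a histopathological reference standard", summarised as sensitivity, specificity, PPV and NPV at primary staging and after neoadjuvant chemotherapy.

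The text after Fig. 1 in the Study flow overview names the reference: "Histopathology of the resected specimens and biopsies will serve as a reference standard for calculating the diagnostic accuracy". It then gives a fallback: "For suspicious lesions not confirmed by histopathology, other imaging modalities (US, MRI, CT), biochemistry, and medical records will be used for classification". FDG PET/CT is not in that list, and the rule is not confined to one tracer.

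The Diagnostic accuracy section gives the fallback again, this time only for suspicious lesions revealed on FAPI PET/CT. Those "lacking histopathological confirmation will be evaluated using available routine diagnostic images ([^18^F]FDG PET/CT, UL, MR, ceCT), medical records, and laboratory tests". FDG PET/CT is the first source named.

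Three other statements bear on which lesions reach the fallback and on what it contains:

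- Study flow overview: "the results of the FAPI PET/CT will not be available to the patient or the treating physician".
- Pathology analysis: "The clinical trial will not influence the amount of biological material collected from the patients".
- Diagnostic accuracy: "ceCTs performed at primary staging and at post-NACT staging is part of the PET/CT procedure and will also be available for the interpreters".

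For the tentative MDT, by contrast, the section on staging and patient management lists "Supplementary imaging results (excluding the FDG PET/CT results" among the material supplied. The tracers are kept apart there. No such separation is stated for lesion classification.

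**The concern.** A test under comparison should not help to decide the truth against which its rival is scored. The lesions that matter most here are positive on FAPI and negative on FDG. FAPI findings are withheld from the treating team and tissue collection follows routine practice, so a FAPI finding cannot prompt sampling. It is plausible that these discordant lesions lack histology more often than others and depend more on the fallback.

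If the negative FDG scan then counts towards benign, a truly malignant FAPI-only lesion is scored as a FAPI false positive. At the same time an FDG miss is rescored as an FDG true negative. Where both scans are positive on a benign lesion, FDG can confirm the FAPI error, and both tracers are credited with a true positive.

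The difference in scope is a second problem. Read literally, the Diagnostic accuracy section classifies unverified lesions only if FAPI showed them. Malignant lesions seen only on FDG and lacking histology would then drop out of the count, which removes FAPI misses.

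The Background criticises earlier studies because most findings beyond the primary tumour could not be compared with histology. An unreconciled fallback brings part of that weakness back.

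**Working it through.** **The two rules side by side**

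| | Study flow overview | Diagnostic accuracy |
|---|---|---|
| Lesions covered | any suspicious lesion without histology | lesions revealed on FAPI without histology |
| FDG PET/CT used | not listed | listed |
| Other sources | US, MRI, CT, biochemistry, records | ultrasound, MR, ceCT, records, laboratory tests |

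The same lesion can be classified differently under the two rules. The plan gives no figure to reproduce: it states neither the share of lesions without histology nor the weight given to FDG. The calculations below therefore show direction and possible size only.

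**Check 1: a simple count for peritoneal lesions**

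From the Background (a cited prospective study): sensitivity 98% for FAPI and 76% for FDG. Assumed: FAPI finds every lesion that FDG finds, and there are 5 FAPI false positives per 100 malignant lesions. Let u be the share without histology and q the share of unverified FAPI-only malignant lesions called benign.

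Per 100 malignant lesions, 76 are positive on both, 98 − 76 = 22 on FAPI only, and 2 on neither.

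- Lost = 22 × u × q
- FDG sensitivity = 76 / (100 − lost)
- FAPI PPV = (98 − lost) / 103

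| u | q | Lost | FDG sensitivity | FAPI PPV |
|---|---|---|---|---|
| 0 | – | 0 | 76/100 = 76.0% | 98/103 = 95.1% |
| 0.10 | 0.25 | 0.55 | 76/99.45 = 76.4% | 97.45/103 = 94.6% |
| 0.30 | 1 | 6.6 | 76/93.4 = 81.4% | 91.4/103 = 88.7% |
| 0.50 | 1 | 11 | 76/89 = 85.4% | 87/103 = 84.5% |

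FDG sensitivity shifts by 0.4 to 9.4 points and FAPI PPV by 0.5 to 10.7 points. The row at u = 0.30 is the worst case for that share, because every unverified FAPI-only malignancy is miscalled. This model has no FDG-only lesions, so it cannot show the opposing bias.

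**Check 2: a model that allows FDG-only lesions**

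Assumed: 200 malignant and 200 benign sites, a 10% false-positive rate for each tracer, tracers independent given the truth, and u = 0.50. Unverified lesions negative on both tracers are not counted. The probability that the FDG result overrides the truth for an unverified FAPI-positive lesion is w. Sensitivities from the Background: 98% v 76% (peritoneal) and 81% v 61% (lymph node).

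Apparent sensitivity difference, FAPI minus FDG:

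| Site (true difference) | Unverified FDG-only lesions | w = 0 | w = 0.25 | w = 0.5 | w = 1 |
|---|---|---|---|---|---|
| Peritoneal (0.22) | classified correctly | 0.220 | 0.197 | 0.171 | 0.116 |
| Peritoneal (0.22) | left out | 0.230 | 0.206 | 0.180 | 0.126 |
| Lymph node (0.20) | classified correctly | 0.208 | 0.174 | 0.136 | 0.052 |
| Lymph node (0.20) | left out | 0.285 | 0.252 | 0.216 | 0.133 |

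Along each row, a greater FDG weight moves the difference towards FDG. Leaving out FDG-only lesions moves it towards FAPI. For lymph nodes with these lesions left out, the result lies above the true 0.20 at w = 0.25 and below it at w = 1.

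The other measures move one way under either treatment of FDG-only lesions. From w = 0 to w = 1, FAPI PPV falls from 0.907 to 0.803 (peritoneal) and from 0.890 to 0.722 (lymph node). For peritoneal lesions with FDG-only lesions classified, FAPI specificity falls from 0.832 to 0.700, and FDG specificity rises from 0.832 to 0.866.

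**The case against.** A reader might infer that the head-to-head comparison as a whole is biased towards FDG, by roughly the 5 points in the u = 0.30 row. The documents do not support that, for four reasons.

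- **Direction.** The literal FAPI-only scope of the Diagnostic accuracy section would favour FAPI sensitivity, and Check 2 shows that this can outweigh the FDG effect. The Study flow overview, if it governs, covers lesions from either tracer and leaves FDG out. This objection stands for the sensitivity difference. It does not remove the shift in PPV and specificity.
- **Mechanism.** No rule says that a negative FDG scan makes a lesion benign. FDG is one source among several, and follow-up of up to 10 years may settle some lesions through the records. This stands: the effect is conditional on the weight given to FDG. But nothing in the text limits that weight.
- **Unverified share.** Patients are judged operable and resectable, surgery aims at complete or optimal cytoreduction, and specimens are labelled by location. Sampling therefore depends also on what the surgeon finds. That FAPI-only lesions are the least sampled is a plausible inference, not a stated fact.
- **Stakes.** The trial is exploratory, has no formal sample size calculation, and already names histopathology as its reference. Lesions with histology are unaffected. This limits the reach of the problem. Yet the Study flow overview places its fallback directly after the reference for accuracy, and nothing shown confines fallback-classified lesions to a secondary analysis.

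ceCT also appears in both the index tests and the fallback, but it is common to both tracers.

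**Conclusion.** The point holds as a defect in what the article states. One section builds the comparator into the reference for FAPI-detected lesions without histology, and another gives a fallback without it and with a wider scope. Insofar as negative FDG scans count towards benign, FAPI PPV and specificity are understated, and FDG sensitivity and specificity are overstated. The net direction for the sensitivity difference is uncertain, because omitting unverified FDG-only lesions would act the other way.

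The size is not derivable. With 10% to 50% of lesions unverified and 25% to 100% of the FAPI-only ones miscalled, all assumed, the shift runs from negligible to about 9 points in FDG sensitivity and 11 points in FAPI PPV. The move from 76% to 81% and from 95% to 89% is an illustrative worst case at 30% unverified, not an estimate.

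**What to change.** Reconcile the Study flow overview and the Diagnostic accuracy section:

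1. Delete FDG PET/CT from the fallback sources.
2. Apply one rule to every unverified lesion seen on either tracer.
3. Withhold both index PET results from the adjudicator, including PET reports in the medical records. Otherwise FDG returns by that route.
4. State that the primary accuracy comparison rests on histology-verified sites.
5. Report fallback-classified and unclassifiable lesions separately.

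The cost is mainly wording, plus the work of screening the records for PET reports. FAPI scans are to be interpreted only after all patients are enrolled, so a change made before reading starts loses no data. The downside is that some FAPI-only lesions will remain unclassified and must be reported as such.
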